## Abstract

**Objectives:**

Myopia is a major public health problem and it is essential to find safe and effective means to control its progression. The study design and baseline data are presented for a one-year prospective, double-masked, crossover, randomized clinical trial evaluating the efficacy of single vision spectacle lenses with concentric rings of slightly aspherical contiguous lenslets technology (SAL) on myopia control.

**Methods:**

One hundred 8- to 13-year old Chinese children with a refractive error of -0.75 D to -4.75 D were assigned to two groups. In Group 1, SAL and single vision lenses were each worn for 6 months, and Group 2 wore the lenses in the reversed order. Primary outcomes are axial length and spherical equivalent of cycloplegic refractive error. Secondary outcomes included corneal thickness, anterior chamber depth, lens thickness, visual acuity, and lens adaptation.

**Results:**

No significant differences in baseline parameters (cycloplegic spherical equivalent, axial length, age) were found between groups (0.49 < *p* < 0.94). All children adapted well to the test lenses and there was no significant difference in visual acuity between the SAL and single vision lenses (*p* = 0.27).

**Conclusions:**

The children in the two well balanced groups had comparable visual acuity and adapted well to the test lenses. These results imply that visual acuity can be well improved by SAL lenses. Clear visual acuity provides the assurance for good compliance in this longitudinal study.

**Supplementary Information:**

The online version contains supplementary material available at 10.1186/s12886-022-02562-0.

## Background

Myopia has become a major public health problem worldwide. In the recentdecades, the prevalence of myopia has gradually increased. The prevalence of myopia and high myopia was 22.9% and 2.7% of the world population in 2000, and it is expected to rise to 49.8% and 9.8%, respectively in 2050 [1]. Compared with other regions, the prevalence of myopia is highest in Asia, especially in East Asia [2–4]. Lin et al. [3] reported that the prevalence of myopia in Taiwan rosefrom 74 to 84% from 1983 to 2000 in 16 to 18 year- old children. Furthermore, the prevalence of high myopia in 18-year-old students increased from 10.9% to 21%.

Excessive progression of myopia has been shown to be associated with sight-threatening complications [5–7]. The odds of complications increase with a higher degree of myopia and greater axial length [8]. Thus, preventing the progression of myopia and slowing down the elongation of the eye at an early stage is vital to avoid later ocular complications.

Several interventions are currently available to slow myopia progression, such as topical administration of atropine and use of orthokeratology (Ortho-K), multifocal contact lenses, or specially designed spectacle lenses. High doses of atropine are effective but associated with significant adverse effects such as photophobia and impaired accommodation. In addition, the significant rebound effect after cessation of high-concentration atropine limits its widespread use [9, 10]. Lower dosages of topical atropine (0.01%) have feweradverse effects; however, the axial length control effect is limited [11]. Ortho-K is effective in myopic refractive error and myopia control [12–14], but the efficacy is significantly associated with corneal shape [15–18]. Recently, many studies have reported that dual-and multifocal soft contact lenses are effective strategies for slowing myopia progression [19–22]. However, potential ocular complications such as conjunctivitis and keratitis [23] limit the large-scale usage of soft contact lenses in myopia control.

On the other hand, spectacle lenses represent a safe and easy-to-administer option for myopia control. Among spectacle lenses, (prismatic) bifocals provide the best myopia control efficacy [24]; however, aesthetics considerations hinder their more extensive usage. Progressive addition spectacle lenses (PALs) are more aesthetic, but their treatment effect is smaller [25–28]. Spectacle lenses with peripheral hyperopic defocus amelioration have minimal, if any, myopia control effects [29, 30]. Recently, introduced spectacle lenses with myopia control segments may be a promising avenue in myopia control combining good efficacy and aesthetics [31, 32].

Hence, a randomized double masked crossoverclinical trial was undertaken to evaluate the myopia control effect of novel spectacle lenses with contiguous slightly aspherical lenslets (SAL).

## Methods

### Study design

This is a prospective, double-masked, crossover, and randomized clinical trial. The duration of the study is 13 months (see Fig. 1 for more details about the timeline of this study), and it consists of 7 visits.

**Fig. 1 Fig1:**
[figure not shown]
Flow chart of the study; M – month(s), W – week(s)

Eligible subjects were randomized into two groups. Group 1 will wear SAL lenses for 6 months, followed by 6 months of wearing single vision lenses. In Group 2, the order in which the lenses are worn is reversed. In this paper, we refer to the spectacles worn during the first 6 months (regardless of lens type) as study equipment 1 and the spectacles worn during the second 6 months (regardless of lens type) as study equipment 2 (Fig. 1). At each visit, all subjects were instructed to wear the study equipment for more than seven hours every day.

The study is being conducted at the Hangzhou Branch of Zhejiang Eye Hospital Affiliated to Wenzhou Medical University. The study and its protocol followed the tenets of the Declaration of Helsinki and were approved by the institutional review board of the Eye Hospital of Wenzhou Medical University. Written informed consent was obtained from participants and their guardians after a detailed explanation of this study and the possible risks and benefits at the first visit. The study is registered at the Chinese Clinical Trial Registry (ChiCTR1900021002, 24/01/2019).

### Study participants

A total of 100 children were recruited from the hospital into this study between January and March 2019. The inclusion criteria were best-corrected visual acuity equal to or better than 1.0, age between 8 and 13 years inclusive, spherical equivalent of cycloplegic autorefraction between -0.75 D to -4.75 D in each eye, astigmatism no more than 1.50 D, anisometropia no more than 1.00 D, and absence of strabismus. Subjects with a history of ocular or systemic disease, history of wearing PALs, or prior myopia control treatment were excluded from participation in the study.

The study was designed to achieve 80% power to detect a minimum difference of 0.27 D with an SD of 0.37 D at 6 months at a 5% level of significance. Using an online sample size calculator by the Clinical & Translational Science Institute33, the theoretical sample size was 42 with a 1:1 sample ratio in each group. Allowing a maximum drop-out rate of 15%, the number to be recruited for each group was estimated to be 50.

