### Secondary outcome measures

Corneal thickness (CT), anterior chamber depth (ACD), and lens thickness (LT) were measuredwith a Lenstar LS900 (Haag-Streit, Koeniz, Switzerland) together with AL. Five measurements were taken, and the average value per eye was used for further data analysis. Distance-corrected visual acuity (DCVA) is evaluated using a standard 100% contrast English Early Treatment Diabetic Retinopathy Study (ETDRS) logMAR chart at 4 m with usual correction or new distance prescription. DCVA is scored using the standard technique of subtracting 0.02 logMAR units for each correctly identified optotype.

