### Between-group comparison of baseline data

Eligible subjects were randomized to two groups of 50 subjects. The mean age was 9.48 ± 1.36 years (range: 8 to 12) in Group 1 and 9.50 ± 1.50 years (range: 8 to 12) in Group 2. There was no significant difference between the groups (t = -0.07, *p* = 0.94).

The two groups were matched for SER and AL. The mean AL was 24.79 ± 0.67 mm (range: 23.35 to 26.59 mm) in Group 1 and 24.89 ± 0.84 mm (range: 23.13 to 26.86 mm) in Group 2. The mean SER was -2.68 ± 0.83 D (range: -1.25 to -4.50 D) in Group 1 and -2.72 ± 0.90 D (range: -1.00 to -4.50 D) in Group 2. There was no significant difference between the groups for AL or SER (t = -0.69, *p* = 0.49 and t = 0.22, *p* = 0.83, respectively). SER and AL were negatively correlated in both groups (Group 1:r = -0.309, p = 0.029; Group 2:r = -0.506, *p* < 0.001; Fig. 2).

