### Lens adaptation

All subjects adapted well to both SAL lenses and single vision lenses (Table 4). The mean DCVA at the dispensing visit was 0.06 ± 0.08 logMAR (range: -0.14 to 0.24 logMAR) in Group 1 (SAL lenses) and 0.04 ± 0.05 logMAR (range: -0.1 to 0.14 logMAR) in Group 2 (single vision lenses, SVL), with no significant difference between the groups (t = 1.11, *p* = 0.27).

**Table 4 Tab4:** Adaptation to the SAL and single vision lenses. *DCVA* Distance-corrected visual acuity. Data expressed as the mean ± SD. Group 1: in phase one for Group 1, the subjects wear the SAL lenses; Group 2: in phase one for Group 2, the subjects wear single vision lenses (SVL)

	SAL	SVL	t value	*p* value
DCVA	0.06 ± 0.08	0.04 ± 0.06	1.11	0.27
Perception of ghost images	1.04 ± 0.20	1.00 ± 0.00	1.43	0.16
Comfort of spectacles	9.68 ± 0.55	9.84 ± 0.42	-1.64	0.11
Clarity of vision	9.70 ± 0.58	9.93 ± 0.25	-2.59	0.01
Vision satisfaction	9.72 ± 0.50	9.91 ± 0.29	-2.32	0.02

For the perception of ghost images, we found no significant difference between the lens types (mean values: 1.04 ± 0.20 for SAL lenses and 1.00 ± 0.00 for SVL lenses; t = 1.43, *p* = 0.16). Similarly, there was no significant difference in the comfort of the spectacles (mean values: 9.68 ± 0.55 for SAL lenses and 9.84 ± 0.42 for SVL lenses; t = -1.64, *p* = 0.11). Regarding clarity of vision and vision satisfaction, small but significant differences were observed between the two lens types. The subjects rated single vision lenses as providing higher clarity of vision (mean values: 9.70 ± 0.58 for SAL lenses and 9.93 ± 0.25 for SVL lenses; t = -2.59, *p* = 0.01) and vision satisfaction (mean values: 9.72 ± 0.50 for SAL lenses and 9.91 ± 0.29 for SVL lenses: 0.19; t = -2.32, *p* = 0.02).

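### Entry acuity of 1.0 does not square with acuity at dispensing in either arm, and the raw, non-significant lens comparison cannot support the claim that SAL leaves DCVA intact

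*Protocol article*

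**What the plan says.** Under Study participants, the protocol article requires "best-corrected visual acuity equal to or better than 1.0". It names no notation, chart, eye or scoring rule for this test.

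Under Secondary outcome measures, DCVA is taken on a "standard 100% contrast English Early Treatment Diabetic Retinopathy Study (ETDRS) logMAR chart". The condition is "logMAR chart at 4 m with usual correction or new distance prescription", and the score is obtained by "subtracting 0.02 logMAR units for each correctly identified optotype". Table 1 schedules DCVA at all seven visits, V1 included.

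Under Study visits and procedures, the washout lenses handed out at V1 match the prescription of the first study spectacles, which are delivered about a month later at V2.

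Under Lens adaptation, DCVA at dispensing is "0.06 ± 0.08 logMAR (range: -0.14 to 0.24 logMAR) in Group 1" (SAL) and "0.04 ± 0.05 logMAR (range: -0.1 to 0.14 logMAR) in Group 2" (single vision). Table 4 gives an SD of 0.06 for the single vision group, where the text has 0.05. The two groups are compared on these raw values (t = 1.11, p = 0.27). From this the Discussion concludes that SAL does not impair DCVA.

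**The concern.** A child who met the entry criterion, read as decimal, should score 0.00 logMAR or lower when fully corrected. At dispensing both group means lie above that, and some children lie far above it. The control lens has no lenslets, so they cannot explain its shortfall. The article prints the criterion, the chart and the results without commenting on the gap.

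Two things are at stake. First, without that child's own baseline value, a child who reads 0.24 logMAR with SAL at V2 cannot be classed as having lost acuity through the lens or as having scored that way on this chart from the start. Second, a claim that the lens costs no acuity rests on a non-significant test of unadjusted values, although a baseline DCVA is scheduled for every child. In Table 4 the same children rate clarity lower with SAL (p = 0.01), so a small acuity cost is not far-fetched.

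**Working it through.** **Inputs.** Entry criterion 1.0 (Study participants), taken as decimal, which is an assumption: logMAR = -log10(1.0) = 0.00. DCVA at V2 (Lens adaptation and Table 4): SAL mean 0.06, SD 0.08, maximum 0.24; single vision mean 0.04, SD 0.05 (text) or 0.06 (Table 4), maximum 0.14. Group size 50 each (Between-group comparison of baseline data); Table 4 prints no n of its own, so 50 is assumed for DCVA. Letter step 0.02 (Secondary outcome measures).

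**1. The article's own test.** t = (0.06 - 0.04) / sqrt((SD1² + SD2²)/50).
- SD2 = 0.06: SE = sqrt((0.0064 + 0.0036)/50) = 0.0141, t = 1.41.
- SD2 = 0.05: SE = sqrt((0.0064 + 0.0025)/50) = 0.0133, t = 1.50.
- Rounding of the means and SDs to 0.01 allows t from 0.66 to 2.43, so the printed 1.11 is compatible, but only within rounding.

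**2. Distance of the means from 0.00.** Mean ± t(0.975, 49) × SD/√50:
- SAL: 95% CI 0.037 to 0.083 (t = 5.3).
- Single vision: 0.026 to 0.054 with SD 0.05 (t = 5.7), or 0.023 to 0.057 with SD 0.06 (t = 4.7).

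**3. Worst values.** Decimal acuity = 10^(-logMAR): 0.24 gives 0.58 and 0.14 gives 0.72. In letters: 0.24/0.02 = 12 and 0.14/0.02 = 7.

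**4. Share worse than 0.00 logMAR.** The article gives no count. The normal model uses Φ(mean/SD), or Φ((mean - 0.01)/SD) to allow for letter steps. The distribution-free minimum (Cantelli) is mean²/(mean² + SD² × 49/50).

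| Group | Normal | Normal, letter steps | Minimum |
|---|---|---|---|
| SAL | 77% | 73% | 36% (at least 19 of 50) |
| Single vision, SD 0.05 | 79% | 73% | 40% (at least 20 of 50) |
| Single vision, SD 0.06 | 75% | 69% | 31% (at least 16 of 50) |

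Allowing for rounding of the inputs, the normal-model range widens to 65-84%, and the lowest of the minima falls to 23%.

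**5. What p = 0.27 leaves open.**
- From the printed difference and t: SE = 0.02/1.11 = 0.018; 0.02 ± 1.98 × 0.018 gives -0.016 to 0.056.
- From the printed SDs (SE 0.0141): 0.02 ± 0.028 gives -0.008 to 0.048.
- If rounding of the difference explains the gap between the two t values: 1.11 × 0.0141 = 0.0157, upper limit 0.0157 + 0.028 = 0.044.

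On all three readings the upper limit is about 0.04 to 0.06 logMAR, or two to three letters.

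**6. Possible gain from adjustment.** With correlation r between V1 and V2 DCVA, adjustment multiplies the SE by about sqrt(1 - r²). The article does not give r. At assumed values of 0.3, 0.5 and 0.7 the factor is 0.95, 0.87 and 0.71.

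**The case against.** The strongest reply is that an offset shared by both arms cancels in a randomised comparison. This stands. The control mean's offset (0.04) is twice the observed lens difference (0.02), which may tempt a reader to infer that the comparison is distorted. It is not: letter-reading ability or a prescription shortfall adds noise to the difference, not bias. The noise is also modest. With an SE of 0.0141, a true difference of about 2.8 × 0.0141 = 0.04 logMAR is detectable with 80% power.

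It is also fair to say that the crossover will let each child be compared in both lenses, so the classification problem is confined to the V2 data reported so far. DCVA is a secondary outcome, and adaptation is judged on four questionnaire items as well. The axial length and refraction analyses are untouched.

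On the remedy, DCVA may be taken with the usual correction, and the article does not say which correction applied at V1. Twenty-seven children reported no earlier detection or correction of myopia. A change from an uncorrected or outdated baseline would measure the new prescription, not the lens. This limits which V1 values can serve.

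Finally, a condensed article may leave the screening chart to the full protocol. Silence on that chart alone would be no finding. The point rests on printed figures that do not fit together and on a conclusion that the printed test does not carry.

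**Conclusion.** On the decimal reading, the entry criterion and the dispensing-visit DCVA do not square. Both means are clearly above 0.00 logMAR, and the worst children are 7 and 12 letters short. The decimal reading is the natural one, but it is an assumption.

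A reader might infer three stronger things that the article does not support:
- **That three quarters of the children are known to miss the entry level.** This is a normal-model estimate (69-79%); the printed values guarantee only about 31-40%.
- **That the two tests are shown to be on different scales.** A different chart, eye or scoring rule would fit, but so would dispensed spectacles against a trial frame, change over the month, or loose application of the criterion. Line scoring alone is not enough: a pass at 3 of 5 letters (assumed) allows about 0.04, not 0.14 or 0.24. The control arm shows only that the lenslets are not the sole cause.
- **That the mean lens difference is biased.** Randomisation balances the offset on average.

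What remains is a comparison with avoidable between-child noise, whose non-significant result leaves a SAL deficit of about 0.05 logMAR open and is nevertheless read as no loss. This is worth changing, but it concerns a secondary outcome.

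**What to change.** - Analyse DCVA with the study lens adjusted for the same child's V1 ETDRS DCVA, which Table 1 already schedules. Use the V1 value taken with the new distance prescription where there is one, and state which correction each V1 value was taken with.
- Once both periods are complete, compare SAL with single vision within child, allowing for period, since the second pair is prescribed from the 5-month refraction.
- Report the lens difference with its 95% CI, and per lens the number of children who lose 0.1 and 0.2 logMAR or more (5 and 10 letters) from a best-corrected V1 value.
- Limit the statement that SAL does not impair DCVA to what that interval supports.
- Reconcile Study participants, Secondary outcome measures and Lens adaptation on the notation, chart, eye and scoring of the entry acuity. Show V1 DCVA and the number of children worse than 0.00 logMAR at V1 and V2. Correct the single vision SD, which is 0.05 in the text and 0.06 in Table 4.

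The cost is a minor reanalysis and some rewording, with no new visit. If V1 DCVA was taken with the usual correction in some children, fewer baseline values can be used. The acuity statement may become slightly less favourable to SAL.

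### The planned 42 per group does not follow from the stated inputs: 0.27 D, SD 0.37 D and 80% power need 31 per group, and 42 gives about 91% power

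*Protocol article*

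**What the plan says.** The whole calculation stands in one paragraph of the protocol article, under Study participants. The target and the assumed variability are given as "80% power to detect a minimum difference of 0.27 D with an SD of 0.37 D at 6 months", "at a 5% level of significance". The result is reported as "the theoretical sample size was 42 with a 1:1 sample ratio in each group", attributed to an online calculator. The last step reads "Allowing a maximum drop-out rate of 15%, the number to be recruited for each group was estimated to be 50".

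Two other sections fix the setting. Prospective data analyses plans an independent-sample t test between the two lens types. Main outcome measures makes cycloplegic spherical equivalent (SER) the only primary outcome measured in dioptres. The calculation therefore appears to concern SER change over the first six months, before the crossover. The paragraph does not say whether the test is one- or two-sided, or whether 0.37 D is a between-subject SD or the SD of a within-subject difference.

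**The concern.** The standardised difference is 0.27/0.37 = 0.73, which is large. A two-group comparison of that size at 80% power needs about 30 per group, and the article reports 42. The excess over 31 is 11 children per group (11/31 = 35%), too much for rounding or for differences between calculators.

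This is the document's only statement of power. As written, a reader cannot tell which of several designs was intended: 80% power for a difference smaller than 0.27 D, 80% power for 0.27 D with a larger SD, or roughly 90% power for 0.27 D with SD 0.37 D. These differ in the effect the trial was meant to detect and in the variability it assumed. Both matter when the six-month result is set against the plan.

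**Working it through.** **Inputs** (Study participants): difference δ = 0.27 D, SD σ = 0.37 D, power 80%, significance 5%, 1:1 allocation, drop-out 15%. Two-sided testing is assumed because sidedness is not stated.

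**The part that reproduces.** 42/(1 − 0.15) = 49.4, rounded up to 50 per group. The drop-out step is correct, and it shows that 42 is a per-group number.

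**The part that does not.** Normal formula:

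n = 2 × (1.960 + 0.842)² × (0.37/0.27)² = 29.5, so 30 per group.

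Solving with the noncentral t distribution, which matches the planned test, gives 30.47, so 31 per group. With 15% drop-out that is 31/0.85 = 36.5, so 37 per group.

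**Power at the stated sizes** (t test, standardised difference 0.730):

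| Per group | Power |
|---|---|
| 21 (if 42 were the total) | 63.6% |
| 42 | 91.1% |
| 50 | 95.1% |

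The normal approximation gives 91.7% at 42.

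**Other readings at 80% power, keeping 0.27 D and 0.37 D:**

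| Reading | n |
|---|---|
| One-sided 5% | 24 per group |
| Paired t, SD of the difference 0.37 D | 17 in total |
| Paired t, SD of the difference 0.37 × √2 = 0.523 D | 32 in total |
| 31 inflated for a rank test (efficiency 0.955 / 0.864) | 33 / 36 per group |
| Two-sided 2.5% (split over two primary outcomes) | 36 (normal) or 37 (t) per group |
| Two-sided 1% | 44 (normal) or 46 (t) per group |

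None gives 42, and the last two already depart from the stated 5%.

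**What comes close to 42 when an input is changed:**

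- Difference 0.23 D, SD 0.37 D, 80% power: 41.6 by t, so 42 per group. Equivalently, 42 per group has 80% power for 0.619 × 0.37 = 0.229 D.
- Difference 0.27 D, SD 0.44 D, 80% power: 42 by the normal formula; 42.7 by t, so 43.
- Difference 0.27 D, SD 0.37 D, 90% power two-sided: 40 by the normal formula; 40.4 by t, so 41.
- The same difference and SD, 95% power one-sided: 41 by the normal formula; 41.3 by t, so 42.

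**The case against.** The arithmetic is not in dispute; its weight and the diagnosis are. First, the error is conservative: the trial enrolled more children than the stated inputs require, enrolment is complete, and no design decision turns on it. That stands. Under each candidate correction above, 42 per group keeps about 80% power or more for 0.27 D. The doubt is about what was planned, not evidence of an underpowered trial.

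Second, a null or borderline result will be read mainly from the estimate and its confidence interval, which use the observed SD. That also stands, and it limits the practical harm.

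Third, 90% power needs 41 per group, one child short of 42, so a mistyped power is as plausible as a mistyped SD (43 by the t test at 0.44 D). This is fair: 90% power should stay on the list of explanations.

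Fourth, writing in 91% power now would be back-calculation, and false if the SD is the wrong input. This bears on the remedy: the wording should be used only once the difference and SD are confirmed.

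None of these points makes the sentence correct. Each candidate explanation needs a stated value to be wrong.

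**Conclusion.** The concern holds. The article states all the main inputs and the result, and they disagree, so this is not detail left to an unseen analysis plan. The required size is overstated by 11 per group, or equivalently the power at 42 is understated by about 11 percentage points (91.1% against 80%).

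The conclusion assumes a two-sided 5% test, a between-subject SD of 0.37 D and the planned independent-sample t test. It survives the one-sided, paired and total-sample readings. Which value is wrong cannot be settled from the document. The correction is worth making, but it is a reporting error on the safe side and does not threaten the trial's ability to detect 0.27 D.

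**What to change.** Keep 50 per group. Recover the values entered in the calculator and correct the sentence accordingly, adding the sidedness, the type of SD, and that the calculation concerns SER in the first-period between-group comparison, if that was the intention.

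- If the difference and SD are confirmed, say that 42 evaluable children per group give about 91% power for 0.27 D with SD 0.37 D (equivalently 80% power for 0.23 D), and that 31 per group would have met 80%.
- If the difference or the SD was mistyped, replace it with the value used and leave the power at 80%.
- If the entries cannot be recovered, say so, and give the power at 42 per group as a recalculation from the published inputs rather than as the original design target.

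The cost is one corrected sentence, with no change to enrolment, visits or analysis.
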